## 2. Materials and Methods

### 2.1. Sample Recruitment

This study will involve 60 BPD patients who will be recruited among outpatients seeking treatment at an Italian community-based Department of Mental Health, after obtaining approval from the Local Ethical Authority. An a priori power analysis, performed with G-Power 3.1 [29], considering a F-ANOVA mixed repeated measures, with a between-subjects factor (tDCS group, 2 levels: sham and real tDCS) and a within-subjects factor (time, 3 levels: T0 = baseline, T1 = during the tDCS protocol, T2 = 10 days after the end of the tDCS protocol; a subsample collected T3 = 3 months after the end of the tDCS protocol were not included in the power analysis), resulted in a sample size of 30 participants (15 per group) to detect reliable outcome measures with α = 0.05, effect size (d) = 0.28, and power = 0.95. Notably, the effect size of 0.28 was based on the effect sizes of previous works from the research group [19,20,21]. We doubled the sample size suggested by the power analysis to account for the number of participants needed in the EMA protocol. While our EMA protocol was more intensive than average, a meta-analysis of response compliance in EMA studies with BPD patients showed that they were tolerant of more intensive prompt schedules and evaluation days, with a 79% compliance rate [29]. Further, we have adopted many design features associated with greater compliance in EMA studies of psychiatric patients, including regular prompt intervals spaced out over a longer period of time [30]. There are power increases as the number of observations increases in a repeated measures design; in the 30-day EMA protocol (T0-T2), participants rated approximately 150 events (5 events/day × 10-day bursts × 3 bursts) (Figure 1). We assumed an average compliance rate of 80% for all EMA prompts (120 observations per participant for T0–T2), thus accounting for missing data. Figure 1 provides a power curve for multilevel models, showing that 60 participants provided adequate power (>0.75) to detect a medium (d > 0.5) effect, assuming an 80% completion rate during T0-T2 with an ICC value of 40%, as per our prior studies [28,31,32,33]. The subsample of participants who agreed to complete a 3-month follow up (we expected 50% of the original sample), assuming a compliance rate of 80% for all EMA prompts, resulted in an additional 40 observations per subsample participant at T3.

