The tDCS device (DC-STIMULATOR, NeuroConn GmbH, Ilmenau, Germany) includes a study mode for a double-blind procedure. Namely, a numeric code (four digits), corresponding to either anodal or sham tDCS, will start the stimulation, thus preventing the awareness of the stimulation condition in both participants and the research assistant—neither of whom is aware of the correspondence between the code and the type of stimulation that will be delivered. More specifically, the research assistant will read on participants’ log files one of two codes for each new participant. Unbeknownst to the research assistant who delivers the tDCS, two codes will trigger anodal tDCS, the other two will trigger sham stimulation. Thus, the proposed study will be a double-blind study, meaning that both patients and investigators involved in the tDCS sessions will be blinded to the stimulation conditions (real or sham tDCS). Before starting the experiment, an investigator different from the one who will apply the tDCS stimulation will set the tDCS parameters for real and sham stimulation by using two different numerical codes. Such codes will be saved in an unmodified mode in the tDCS device so that at the beginning of each session, according to the randomization, active or sham stimulation will be chosen by only considering their corresponding codes. The unmodified mode rules out the possibility that codes and stimulation parameters will be changed during the experiment. To further check for participants blindness, at the end of the treatment, a questionnaire inquiring about the participant’s guess on the real vs. sham condition assignment and eventual side effects of the stimulation will be administered.

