tDCS will be delivered during the *Cyberball* paradigm, a virtual ball-tossing game that reproduces different levels of social inclusion by manipulating the percentage of tosses that participants receive from two other computer-controlled co-players. After about five minutes of stimulation, participants will play first the social inclusion (33% of throws received), then the social exclusion (10% of throws), then the over-inclusion (45% of throws) conditions of the game. The order of these experimental phases is fixed, ensuring that the game ends with the over-inclusion condition, which is typically not associated with negative emotions in BPD [10,13], for ethical reasons. The choice in the study design to deliver tDCS during the *Cyberball* stimulation design is based on recent evidence on the state-dependency of tDCS, pointing to the opportunity to timelock the stimulation to a concurrent activity involving the stimulated target area in order to achieve specific effects [54,55,56]. tDCS experiments will be conducted by trained investigators and participants can stop the stimulation at any time if they want to. TDCS is not invasive, with few adverse effects, mostly consisting of an itching sensation during the ramp-in phase of the current [57]. At the end of the tDCS treatment, participants will complete a questionnaire to investigate the eventual side effects and to control for tDCS blinding effectiveness [58]. Checking blindness effectiveness indeed becomes more crucial when multiple sessions are included in a protocol. In particular, the questionnaire [58] explores participants’ beliefs on tDCS condition assignment. The frequency of correct vs. incorrect guesses will then be compared between the real vs. sham control group by means of a Chi-square test.

All subjects will be extensively debriefed upon completion of the study. They will receive detailed information about the tDCS protocol and its purpose and will have the opportunity to have their data deleted should they so wish.

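### The planned blinding test compares correct-guess rates between arms, which is not the blinding hypothesis: it cannot see equal unblinding of both arms and can flag a shared lean in guessing as unblinding

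*Protocol article*

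**What the plan says.** Section 2.4 of the protocol article says that at the end of treatment participants receive "a questionnaire inquiring about the participant’s guess on the real vs. sham condition assignment". The same section gives the purpose: "participants will complete a questionnaire to investigate the eventual side effects and to control for tDCS blinding effectiveness". It then names the variable, the comparison and the test: "The frequency of correct vs. incorrect guesses will then be compared between the real vs. sham control group by means of a Chi-square test". It also gives weight to the check: "Checking blindness effectiveness indeed becomes more crucial when multiple sessions are included in a protocol".

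Section 2.4 describes no other analysis of the guesses: no table of guessed condition by actual arm, no comparison with chance and no blinding index. Section 2.5, on the statistical analysis, does not mention blinding. No decision rule or consequence is attached to the test.

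**The concern.** Participants are unblinded to the extent that their guess depends on the arm they are in. The planned test asks whether being *correct* depends on the arm, which is a different question. If patients on real stimulation recognise it and patients on sham recognise sham equally often, correctness is the same in both arms and the test has nothing to find. If guesses carry no information about the arm but most patients say 'real', correctness is high in the real arm and low in the sham arm, and the test can turn significant although blinding held.

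This matters because the primary outcome in section 2.3 is self-rated emotion, on which expectation can act directly. Sham differs from real stimulation in duration (20 s against 20 min) and is repeated over 10 sessions. Recognition in both arms would be a serious threat to the treatment contrast, and when it is equal in the two arms this test is blind to it. A non-significant result could then be read as evidence that blinding held.

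**Working it through.** The article gives no figure for the blinding check, so there is none to reproduce. The check compares the planned test with a test of guess by arm on the same data.

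**Inputs**
- Total sample: "This study will involve 60 BPD patients" (section 2.1).
- 30 per arm: an assumption. Section 2.1 states equal groups only for the power calculation (15 per group).
- Guess: binary, real or sham, as section 2.4 describes it.
- Significance level 0.05: an assumption, since the article states it only for the power analysis.
- Guess rates: illustrative assumptions, shown over a range.

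**The two hypotheses.** Let q_real and q_sham be the shares guessing 'real' in each arm. The correct-guess rates are q_real in the real arm and 1 − q_sham in the sham arm.
- Blinding: q_real = q_sham.
- Null of the planned test: q_real = 1 − q_sham.
- Both hold only if q = 1 − q, that is q = 0.5 in both arms.

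**Formula.** For a 2×2 table with rows (a, b) and (c, d), Pearson chi-square without continuity correction is N(ad − bc)² / (product of the four margins), with N = 60.

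**Both arms equally unblinded, 24/30 correct in each**
- Planned table, correct/incorrect by arm: (24, 6) and (24, 6). ad − bc = 144 − 144 = 0, so chi-square = 0 and p = 1.
- Guess by arm, 'real'/'sham': (24, 6) and (6, 24). 60 × (576 − 36)² / 30⁴ = 60 × 291,600 / 810,000 = 21.6, p = 3×10^-6.

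**Perfect blinding, 80% in each arm guess 'real'**
- Planned table: (24, 6) and (6, 24), chi-square = 21.6, p = 3×10^-6 (1.1×10^-5 with Yates correction).
- Guess by arm: (24, 6) and (24, 6), chi-square = 0, p = 1.

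**Range of scenarios, 30 per arm, uncorrected**

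| Scenario | Correct, real / sham | Planned test | Guess by arm |
|---|---|---|---|
| Both unblinded, 70% | 21 / 21 | 0, p = 1 | 9.6, p = 0.002 |
| Both unblinded, 80% | 24 / 24 | 0, p = 1 | 21.6, p = 3×10^-6 |
| Both unblinded, 90% | 27 / 27 | 0, p = 1 | 38.4, p = 6×10^-10 |
| Blind, 60% lean to 'real' | 18 / 12 | 2.4, p = 0.12 | 0, p = 1 |
| Blind, 70% lean | 21 / 9 | 9.6, p = 0.002 | 0, p = 1 |
| Blind, 80% lean | 24 / 6 | 21.6, p = 3×10^-6 | 0, p = 1 |
| Real arm unblinded, sham arm at 50% | 27 / 15 | 11.43, p = 0.0007 | 11.43, p = 0.0007 |

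**Rejection probability at 0.05**, by exact binomial enumeration:
- True correct rate of 70%, 80% or 90% in both arms: planned test about 0.05 throughout; guess by arm 0.90, above 0.99 and above 0.99.
- Perfect blinding with a 60%, 70% or 80% lean: planned test 0.35, 0.90 and above 0.99; guess by arm about 0.05 throughout.

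**Per-arm index.** With a binary guess, Bang's index is 2 × (proportion correct) − 1. It separates the cases: +0.60 / +0.60 when both arms are 80% correct, against +0.60 / −0.60 for a pure 80% lean.

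**The case against.** Four objections deserve an answer.

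1. *The check is ancillary.* This stands. The result does not enter the model in section 2.5 and triggers no exclusion or change of analysis. A reader might infer that the primary result is compromised; the article does not support that, because the estimate is the same whatever this chi-square shows. Nor does the article set a pass/fail rule. Treating non-significance as a pass is the usual reading, not a stated one.

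2. *Nothing is lost.* With a binary guess, the correct and incorrect counts by arm contain the guess-by-arm table, so a reader given the counts could compute the right test. This stands and makes the error recoverable. It does not make the planned p-value answer the right question.

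3. *The test is not always wrong.* This also stands. A reader might infer that it can never detect unblinding, or that it always condemns good blinding when guesses lean. Neither holds. If one arm is unblinded and the other guesses at 50%, both tables give the same answer. A false alarm depends on the size of the lean: 60% is usually not significant, and at 19/30 against 11/30 the result turns on the continuity correction (p = 0.04 without, 0.07 with).

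4. *The detail may be in the full protocol or analysis plan.* This does not help. The article does not leave the method open; it states the variable, the comparison and the test.

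**Conclusion.** The sentence is wrong as written and should be fixed. The planned test has a null that agrees with blinding only when guesses split evenly. Its main weakness is equal unblinding of both arms, where it rejects about 5% of the time however high the common correct rate (70% to 90% examined), while a guess-by-arm test on the same data rejects with probability 0.90 or more. Its second weakness is a shared lean in guessing, where its false-alarm probability rises from 0.35 at 60% to 0.90 at 70%.

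The algebra needs no assumption beyond a binary guess. The figures rest on 30 per arm, a 0.05 level and illustrative guess rates; the article predicts no guess rates. The consequence lies in how the trial's blinding, and so its self-reported outcome, is interpreted, not in the primary estimate.

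**What to change.** Replace the sentence in section 2.4 so that:
- guessed condition (real or sham) is cross-tabulated by actual arm and tested by chi-square;
- each arm has a blinding index (for example Bang's) or its correct-guess rate compared with 50%, with a 95% confidence interval;
- the counts themselves are reported.

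The cost is one or two sentences before analysis, using guesses already planned.

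Two additions are not part of this fix. A 'don't know' category should be tabulated only if the questionnaire already offers it; the article describes a real-or-sham guess, and adding an option would change the instrument. A primary contrast adjusted for or stratified by the guess is not needed and, if done, should be labelled exploratory: the guess is taken at the end of treatment, after randomisation, and may reflect perceived benefit, so conditioning on it could remove part of a true effect or introduce bias. For the same reason, an association between guess and arm should be reported with the caution that it may arise partly from benefit and not only from recognising the stimulation.

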### 2.5. Statistical Considerations and Data Analysis

Given the nested nature of the variable explored in the present study, the primary aim of the study will be examined by means of a 3-level multilevel model as follows: Level-1 for within-subject variability, Level-2 for the different assessment times (T0, T1, T2, T3), and Level-3 (between-group variability) for the tDCS experimental condition (real anodal tDCS vs. sham tDCS). This approach allows us to account for within-person variability across time, and between-subjects and between-conditions variability.

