## Abstract

Background: Borderline Personality Disorder (BPD) is a debilitating mental health condition characterized by emotional dysregulation and interpersonal dysfunction, with perceived social rejection exacerbating these issues. Emerging evidence suggests that a single session of transcranial direct current stimulation (tDCS) over the right ventrolateral prefrontal cortex (rVLPFC) may decrease the unique tendency of BPD patients to feel rejected even when socially included during a laboratory task. Objectives: This protocol outlines a double-blind, sham-controlled study evaluating the longitudinal effects of repeated anodal tDCS over the right ventrolateral prefrontal cortex (rVLPFC) on rejection-related emotions (RRE) during real-life social interactions in individuals with BPD. Methods: Sixty BPD patients will be randomized to receive real or sham tDCS across 10 daily sessions, coupled with an ecological momentary assessment (EMA) protocol capturing emotional and behavioral responses to real-life social interactions over four timepoints: baseline, during treatment, ten days post-treatment, and three months post-treatment. Primary outcomes include changes in RRE, with exploratory analyses examining feelings of social connection, aggressive tendencies, trust toward others, and interpersonal and affective dynamics. Multilevel modeling will assess temporal and group-level effects. Expected Results and Impact: This study aims to establish the efficacy of tDCS in reducing BPD patients’ negative emotional response in real-life social situations and to determine whether such effects are maintained in time. The findings could advance the clinical application of tDCS as an adjunctive intervention to alleviate social–emotional impairments in BPD, addressing gaps in current treatment approaches and guiding future research into the neural mechanisms of social emotion regulation.

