Based on previous evidence that among HC anodal tDCS over the rVLPFC decreases aggressive reactions following social exclusion [20], and that BPD patients feel disconnected by others even in including and over-including scenarios [10] and exhibit extensive impairments in trust processes [27], the EMA protocol will also assess participants’ momentary feelings of social connection and trust toward others, their level of aggressive tendencies, and their perception of their own and their interaction partner’s behavior.

In our prior work, we showed the utility of EMA to evaluate affective and interpersonal changes in patients with BPD treated in psychotherapy, suggesting not only that the occurrence and volatility of daily negative affects decreased over time periods but also that this was accompanied by shifts in interpersonal perceptions [28]. BPD patients (N = 45) made simple ratings of their perceptions of interpersonal warmth/dominance (i.e., is the behavior friendly or unfriendly, agentic or passive?) and affect valence/arousal (i.e., is the emotion happy or sad, intense or quiet?) in both themself and others; multilevel models examined shifts in covariations between these dimensions over the time period during an intervention. Related to the present study, over the course of treatment, BPD patients’ momentary perceptions of others as being more affectively aroused and interpersonally dominant was increasingly connected to seeing them as more friendly. Put differently, the tendency to view an interpersonal event as warm and friendly was associated with a wider range of other’s behaviors and affects, now including even those perceived to be more emotionally intense and agentic. Thus, EMA provided a powerful tool for demonstrating whether experiences of warmth/closeness were associated with highly contextual versus broad interpersonal experiences, as well as shifts in those associations over time via intervention.

Our main hypothesis is that participants receiving the actual tDCS protocol will report decreased RREs over time periods during daily interpersonal interactions (significant change T0–T1, sustained in T2) than participants receiving the sham protocol. We will also explore whether this decrease is also sustained 3 months after the end of the tDCS protocol (T3).

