### 2.4. Transcranial Direct Current Stimulation (tDCS) Protocol

Participants will be randomly assigned to two stimulation conditions: anodal (real) or sham tDCS over the rVLPFC. The tDCS treatment, either real or sham, will last 10 working days and comprise 20 min daily sessions. The stimulation will be applied at an intensity of 1.5 mA, with electrodes of 25 cm^2^ (anode, current density of 0.06 mA/cm^2^) and 35 cm^2^ (cathode, current density 0.042 mA/cm^2^) in line with the safety standards of tDCS [24]. We opt for differently sized electrodes to increase the focality of the stimulation [24]. In the sham modality, all the stimulation parameters (electrode sizes and montage, current intensity, number of sessions) will be kept identical, except for the stimulation duration, which will last only 20 s, with 30 s of rump-in/out as in the real condition to maintain the same physical sensations, thus keeping the participants blind to the tDCS condition [24,49]. An intracephalic montage will be adopted, with the anode placed over the rVLPFC, while the cathode will be placed on the contralateral supraorbital region.

We opt for an intracephalic montage based on prior research on tDCS clinical use [50,51], and to maintain consistency with the montage and tDCS parameters that effectively reduced pain-related emotions in our previous work [19,20,52]. The same electrode positioning procedure, based in the EEG 10-20 system of our previous studies [19,20,52], will be employed. Specifically, the anode will be positioned over F6 (MNI coordinates: 58, 30, 8), which corresponds to the rVLPFC. The effectiveness of such a montage to target the rVLPFC has been tested employing the free software COMETS v.1.04 (http://www.COMETStool.com, accessed on 15 March 2025) [53] to run a computational model of the current flow (figure below taken from Riva et al., 2017 [52]). This model showed that the strongest electric field was concentrated around the cortical area beneath the target electrode (Figure 3).

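### The stated levels of the primary three-level model leave out the participant and put the two-arm condition at the top, so the hierarchy needs to be restated

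*Protocol article*

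**What the plan says.** Section 2.5 states that "the primary aim of the study will be examined by means of a 3-level multilevel model as follows" and then lists every level. The lower two are given as "Level-1 for within-subject variability, Level-2 for the different assessment times (T0, T1, T2, T3". The top one is described in these terms: "Level-3 (between-group variability) for the tDCS experimental condition (real anodal tDCS vs. sham tDCS". The sentence after the list reads: "This approach allows us to account for within-person variability across time, and between-subjects and between-conditions variability".

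Other sections bear on how this should be read:

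- **Unit of randomisation.** Section 2.4: "Participants will be randomly assigned to two stimulation conditions: anodal (real) or sham tDCS over the rVLPFC". The Abstract gives the number: "Sixty BPD patients will be randomized to receive real or sham tDCS across 10 daily sessions".
- **Reports per person.** Section 2.1 plans on "120 observations per participant for T0–T2", which is 40 in each 10-day period.
- **Clustering.** Section 2.1 and the caption of Figure 1 use an ICC of 0.40 for the multilevel power curve.
- **Hypothesis.** The Introduction expects a larger fall in rejection-related emotions with real than with sham stimulation, specified as "significant change T0–T1, sustained in T2".

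No other section restates or corrects the list of levels.

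**The concern.** In a multilevel model the levels name the units whose variation is modelled. Here those units are EMA reports, assessment periods and people. The list has no entry for people, although each person supplies about 120 correlated reports and treatment was assigned to people.

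The list instead has condition at the top. Condition has two values, both fixed by design. A variance between two units would rest on one degree of freedom, and on none once condition is also a fixed effect. Condition is a predictor that varies between participants; it is not a level.

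This is more than brevity. The article sets out a complete hierarchy, and that hierarchy cannot deliver the between-subjects variability that its next sentence promises. An analyst who followed it could treat reports from the same person as independent. The stated error rate of the primary test would then not be assured.

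**Working it through.** **Inputs from the protocol article.** There are 60 participants. Each gives 120 reports over T0–T2, so 120/3 = 40 per period. The ICC is 0.40.

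**Assumptions.** Allocation is 30 per arm (the power analysis in Section 2.1 uses equal groups). Total variance is 1. The ICC is read as the participant share of that variance, 0.40. The participant-by-period variance, tau, describes how much people differ in their change between periods. It is not in the documents and is varied from 0 to 0.20. The residual variance is 0.60 − tau.

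**1. The plan's own power figure.** Section 2.1 claims power above 0.75 for d > 0.5. With participants as clusters and tau = 0, the SE of the overall difference between arms is sqrt((4/60) × (0.40 + 0.60/120)) = 0.164. At d = 0.5 on the total-SD scale this gives power of 0.86, which agrees with the claim. If d were scaled on the SD of participant means, power would be 0.49. The article does not give the scale and the curve is not shown, so an exact match cannot be tested. The planning inputs do fit a model in which participants are the clusters.

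**2. The T0–T1 difference in change without participants.** The literal model is approximated by fixed condition-by-period means with independent errors. Each of the four cell means rests on 30 × 40 reports:

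SE without participants = sqrt(4 × 1/(30 × 40)) = 0.0577, whatever tau is.

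**3. The same contrast with participants.** The participant's constant part cancels in the change:

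SE with participants = sqrt((4/60) × 2 × (tau + (0.60 − tau)/40)).

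Type I error of the test without participants = 2 × (1 − Phi(1.96 × SE without / SE with)).

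| tau (assumed) | SE with participants | SE without | Type I error |
|---|---|---|---|
| 0 | 0.0447 | 0.0577 | about 1% |
| 0.05 | 0.0922 | 0.0577 | about 22% |
| 0.10 | 0.1225 | 0.0577 | about 36% |
| 0.20 | 0.1673 | 0.0577 | about 50% |

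Simulation with 4,000 trials per setting gave 1.1%, 21%, 35% and 50%. A separate simulation of 1,500 trials per setting gave 1.3%, 22%, 37% and 54%. In the second simulation, tests on each participant's own change kept the error at about 5% to 6%.

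**4. Where the two SEs agree.** Setting tau + (0.60 − tau)/40 = 1/40 gives 0.975 × tau = 0.01, so tau is about 0.010. Below that value the test without participants is conservative. Above it the test rejects too often.

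**The case against.** The strongest reply is that the list is shorthand for the variable entering at each level: reports, periods, and participants with condition as their predictor. The surrounding text supports this. The next sentence mentions between-subjects variability, a within-subject level presupposes subjects, and the power work counts observations per participant with an ICC of 0.40. This stands as evidence of intent. It does not make the printed list right, and nothing else in the article corrects it.

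A second reply is that step 2 does not fit the literal model. With condition and period as random levels of a few units each, a condition effect would be inestimable or tested on almost no degrees of freedom. That is also correct. The figures show what omitting participants can do; they do not predict the trial's result.

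Two stronger readings are tempting:

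- **A grossly inflated primary test.** The design effect for the arm difference averaged over T0–T2 is 1 + 119 × 0.40 = 48.6. The SE would be too small by a factor of sqrt(48.6) = 7.0, and the type I error would be about 78%. But that average includes the baseline period and is not the hypothesis. For the change contrast in the Introduction, the error may lie below, at or above 5%.
- **A missing condition-by-time term.** Section 2.5 does not name one. The hypothesis in the Introduction and the group-by-time design in Section 2.1 imply it, nothing excludes it, and an article may leave such a term to the analysis plan.

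**Conclusion.** The point holds as a wrongly stated specification. Section 2.5 names no participant level, makes a two-valued fixed condition the top level, and so contradicts both its own next sentence and the ICC of 0.40 behind the power curve. The likely cause is loose wording, since participant clustering seems intended.

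If the list were followed and participants left out, the standard errors would not be valid. For the T0–T1 difference in change the illustrative type I error runs from about 1% to about 50%. This rests on 30 per arm, 40 reports per period, a participant share of 0.40, independent errors, and a participant-by-period variance of 0 to 0.20. That last quantity alone decides whether the test is conservative or anti-conservative, and the documents do not give it. The documents therefore support saying that the error rate is uncontrolled, but not saying in which direction or by how much.

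**What to change.** Restate the hierarchy in Section 2.5 and carry it into the analysis code:

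- **Level 1:** EMA report.
- **Level 2:** assessment period within participant, with a random effect.
- **Level 3:** participant, with a random intercept.
- **Fixed effects:** condition as a participant-level predictor, period as a categorical factor, and their interaction.
- **Tests of the main hypothesis:** the condition-by-period contrasts T1−T0 and T2−T0.

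Small-sample degrees of freedom (Satterthwaite or Kenward–Roger) and equal T0 means across the randomised arms are optional refinements and are not needed to correct the error. The cost is rewording and code, with no new data and no change to trial conduct.
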